### Audit of interventions and activity

Primary care teams in the intervention practices will be required to send all clinicians and the practice manager to the educational sessions. Further educational sessions will be provided to clinical staff newly recruited during the study period as the need arises. GPs and nurses in intervention and control practices will record patients who present with insomnia and their use of sleep assessment and problem focused therapy techniques using practice computer systems. The content and usefulness of training will be assessed using questionnaires to those in receipt of training. Intervention and control practices will be audited on implementation of the educational intervention by measuring use of assessment and CBTi techniques used by undertaking a weekly computer Read codes audit of all patients recorded with insomnia as well as asking patients through telephone interviews. A sample of up to 4 patients and practitioners from each practice will be invited for a short telephone interview (20 minutes) to understand in more depth the interventions that have been delivered and received as well as perceptions towards these. The interview will determine fidelity to the intervention in study practices and contamination in the control practices and therefore will not be blinded.

### Outcomes

The ***primary outcome measure ***will be global sleep quality as measured by PSQI at baseline and at 0, 4, 8 and 13 weeks.

***Secondary outcomes ***will be measured at baseline and at 0,4,8 and 13 weeks and will include the effect of the intervention on sleep outcome measures assessed with PSQI and sleep diaries [23]: self reported Sleep Onset Latency (SOL, how long it takes to fall asleep), Wake time After Sleep Onset (WASO, total hours awake at night after one has fallen asleep), total Time In bed (TIB) and Sleep Efficiency (SE). Sleep Efficiency, expressed as a percentage, is calculated as follows: SE = (100-[(SOL + WASO/TIB) × 100]). Research has shown that these subjective measures of sleep reflect subjective treatment-related improvements.

We will also measure daytime sleepiness (Epworth sleepiness scale),[24] anxiety and depression using the Beck Depression Inventory,[25] health-related quality of life using EuroQol EQ-5D,[26] psychological outcome profile (PSYCHLOPS)[27] and frequency of use and mean dose of hypnotic medication. Patients will also keep a Data Record Book (DRB) to record any adverse effects that they might experience during the treatment period. Cost-effectiveness will be assessed using the methods below.

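### The Sleep Efficiency formula has a misplaced bracket: only WASO is divided by time in bed, so this secondary outcome comes out wrong, unit-dependent and sometimes negative

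*Protocol article*

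**What the plan says.** In the Outcomes section, the protocol article lists four diary-type sleep measures among the secondary outcomes. The first is latency, given as "self reported Sleep Onset Latency (SOL, how long it takes to fall asleep"). The second is WASO, which the section describes as a number of hours spent awake once sleep has begun. The third and fourth are TIB, with no unit stated, and SE. Of the secondary measures as a group, the section says that they "will be measured at baseline and at 0,4,8 and 13 weeks and will include the effect of the intervention on sleep outcome measures".

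SE is the only one of the four given as a derived quantity. The text introduces the rule with "Sleep Efficiency, expressed as a percentage, is calculated as follows" and then prints "SE = (100-[(SOL + WASO/TIB) × 100", after which the brackets close. The brackets balance and no text is missing. No other section gives a different formula or a worked value. The Data analysis section says the secondary outcomes will be analysed in a similar way to the primary outcome.

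**The concern.** Under ordinary operator precedence, the division inside the round brackets applies to WASO alone. SOL is a length of time and WASO/TIB is a pure number, so their sum has no consistent unit, and multiplying by 100 does not make it a percentage of time in bed. The evident intent is that the two wake components are added first and the total is divided by TIB, which needs the bracket to close after WASO.

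At stake is a named secondary outcome with an explicit derivation rule. If SE were programmed from this text, large negative values would probably be noticed. The more troublesome case is SE computed in hours, the only unit the section mentions (WASO is "total hours awake at night after one has fallen asleep"). Many results would then fall between 0 and 100 and look credible while being wrong. The Study design section says the pilot is to test the integrity of the protocol, the choice of outcomes and the data collection procedures before a definitive trial, so a wrong rule could carry forward.

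**Working it through.** **Inputs from the protocol article (Outcomes).** The formula as printed; SE is a percentage; SOL, WASO and TIB are all durations; WASO is described in hours; no unit is given for SOL or TIB.

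**Inputs assumed.** The article gives no diary values and no worked SE, so there is no figure of its own to reproduce. I assume TIB 8 h, SOL from 0.25 to 2 h and WASO from 0.5 to 1.5 h, with one case of WASO 3 h for the ranking check.

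**Formulas.**
- Printed: SE = 100 − (SOL + WASO/TIB) × 100
- Bracket moved: SE = 100 − ((SOL + WASO)/TIB) × 100

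**One case in full: SOL 45 min, WASO 60 min, TIB 480 min.**
- Bracket moved: 100 − (105/480) × 100 = 100 − 21.875 = 78.125%. The same values in hours give the same answer: 100 − (1.75/8) × 100.
- Printed, in hours: 100 − (0.75 + 1/8) × 100 = 100 − 87.5 = 12.5%.
- Printed, in minutes: 100 − (45 + 60/480) × 100 = 100 − 4512.5 = -4412.5%. Using minutes for SOL but hours for WASO and TIB gives the same value, because WASO/TIB is unchanged.

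**Over the assumed range, TIB 8 h.**

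| SOL (h) | WASO (h) | Bracket moved | Printed, hours | Printed, minutes |
|---|---|---|---|---|
| 0.25 | 0.5 | 90.6% | 68.75% | -1406.25% |
| 0.5 | 1 | 81.25% | 37.5% | -2912.5% |
| 0.75 | 1 | 78.1% | 12.5% | -4412.5% |
| 1 | 1 | 75.0% | -12.5% | -5912.5% |
| 1.5 | 1.5 | 62.5% | -68.75% | -8918.75% |
| 2 | 1 | 62.5% | -112.5% | -11912.5% |

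**Where it turns negative.** The printed SE is below zero when SOL > 1 − WASO/TIB. In hours, with WASO 1 h and TIB 8 h, that is SOL > 1 − 0.125 = 0.875 h, or 52.5 min. With SOL in minutes, any SOL of 1 minute or more gives 100 − (1 + WASO/TIB) × 100 = −100 × WASO/TIB or lower, so zero or below for everyone in practice.

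**Weighting.** In the printed rule SOL has coefficient 100 and WASO has 100/TIB. Their ratio equals TIB in the unit used: 8 to 1 in hours at TIB 8 h, 480 to 1 in minutes. With the bracket moved, both have coefficient 100/TIB.

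**Ranking, in hours at TIB 8 h.**
- Patient A, SOL 0.25 h and WASO 3 h. Bracket moved: 100 − (3.25/8) × 100 = 59.4%. Printed: 100 − (0.25 + 0.375) × 100 = 37.5%.
- Patient B, SOL 0.75 h and WASO 0.5 h. Bracket moved: 100 − (1.25/8) × 100 = 84.4%. Printed: 100 − (0.75 + 0.0625) × 100 = 18.75%.

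B sleeps the larger share of the time in bed, yet the printed rule places B below A.

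**The case against.** The best defence is that this is a slip that nobody would follow. The text names both wake components, time in bed and a percentage scale, so the intent is plain, and an analyst who obtained -4412.5% would not report it. The fault may have arisen in typesetting, and the full protocol or the analysis code may be right. SOL, WASO and TIB are separately listed outcomes, so SE can be recomputed at any time. Much of this stands, and it bears on how serious the error is. It does not remove the error: the article states a calculation rule, the rule is wrong as stated, and values computed in hours need not expose themselves.

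A reader might infer more than the article supports:
- **Every patient gets an impossible value.** In hours, the case worked above gives 12.5%, which is wrong but possible. Negative values in hours need longer latencies.
- **The arm difference would be driven almost entirely by SOL.** That fits the minutes reading only. In hours at TIB 8 h, if the arms differed by d in SOL and 2d in WASO, the contributions would be 100d and 100 × 2d/8 = 25d, so WASO would still supply 25/125 = 20% of the difference.
- **The absent units for SOL and TIB are a second error.** An article can leave that detail to the full protocol or the diary, and with the bracket moved SE does not depend on the unit so long as all three share one.

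**Conclusion.** The formula is wrong as printed. It divides only WASO by TIB, and its result depends on the time unit. At the assumed 45, 60 and 480 min it returns 12.5% (hours) or -4412.5% (minutes) in place of 78.1%. In hours at TIB 8 h it weights SOL 8 to 1 over WASO and can reverse the order of two patients. The misplaced bracket follows from the text alone. The sizes rest on my assumed diary values, and how many trial patients would have a latency beyond 52.5 min cannot be known from the article. Long latencies are plausible, since the Inclusion criteria require difficulty in starting or maintaining sleep.

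It would be tempting to treat this as a threat to the trial's conclusions. The article does not support that. The primary outcome is the global PSQI, the sample size rests on a PSQI difference, and the study is a four-practice pilot in which SE can be re-derived from its recorded components. It is a minor correction to one secondary outcome.

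**What to change.** Replace the formula in the Outcomes section with SE = 100 − [((SOL + WASO)/TIB) × 100], and add that SOL, WASO and TIB are to be in one common time unit. Any unit will do, so hours, as already used to describe WASO, can stay. The correction does not require changing the source of the measures, which the section gives as the PSQI and sleep diaries. Confirm that the full protocol, any analysis plan and the analysis code carry the corrected form, and recompute any SE values already derived from the printed one.

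The cost is one line of text and one check of the code. Design, data collection, sample size and the primary analysis do not change.

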## Abstract

**Background:**

Sleep problems are common, affecting over a third of adults in the United Kingdom and leading to reduced productivity and impaired health-related quality of life. Many of those whose lives are affected seek medical help from primary care. Drug treatment is ineffective long term. Psychological methods for managing sleep problems, including cognitive behavioural therapy for insomnia (CBTi) have been shown to be effective and cost effective but have not been widely implemented or evaluated in a general practice setting where they are most likely to be needed and most appropriately delivered. This paper outlines the protocol for a pilot study designed to evaluate the effectiveness and cost-effectiveness of an educational intervention for general practitioners, primary care nurses and other members of the primary care team to deliver problem focused therapy to adult patients presenting with sleep problems due to lifestyle causes, pain or mild to moderate depression or anxiety.

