We could find no published evidence on the costs of poor sleep in the UK. However in the US the costs (direct, indirect and related) of insomnia have been estimated at US$30 to 35 billion per annum (1994 US$) [12] and in Australia AUS$7494 million (2004 AUS$) of which 53% was accounted for by work-related injuries (net of health costs), private motor vehicle accidents (net of health costs) and productivity losses associated with sleep disorders.[13] The review by Martin et al.[4] made three research recommendations encompassing the need for more accurate costs for patients with different types of insomnia related diagnosis, an estimate of the health utilities associated with particular insomnia diagnoses and their treatments and finally to undertake cost utility analyses of treatments for insomnia to encourage resource allocation to this area.

We have shown in modelling studies involving patients, practitioners and practices that despite patients trying various self-help remedies and sometimes expecting a prescription when presenting with sleep problems, they also welcome a consultation approach which includes careful assessment and advice about non-pharmacological methods rather than a prescription. [14-16] Practitioners are generally positive towards finding new approaches that enhance their skills in non-pharmacological management methods. Brief psychological/behavioural methods[17] have also been shown to be effective in one previous limited evaluation of effectiveness.[18]

The objective of this paper is to describe the design of a pilot cluster randomised controlled study, the aim of which is to test procedures and collect information in preparation for a larger definitive cluster-randomised trial. The definitive study will determine the effectiveness and cost-effectiveness of an educational intervention for general practitioners, primary care nurses and other members of the primary care team to deliver problem focused therapy to adults patients presenting with sleep disturbance due to primary insomnia or specific comorbid insomnia due to pain or mild to moderate depression and anxiety compared to usual care (general advice on sleep hygiene and pharmacotherapy).

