## Methods

### Aims

Our main aim for the pilot study is to test procedures and collect information in preparation for a larger definitive cluster-randomised trial. The definitive trial will investigate the effectiveness and cost-effectiveness of a brief practice-based educational intervention (2 × 2 hours) for practice teams (GPs, primary care nurses and practice managers) to provide problem focused therapy for insomnia in adults involving the use of sleep assessment tools (assessed with standardised instruments and sleep diaries) and modified CBTi on sleep outcomes compared to usual care (general advice on sleep hygiene and pharmacotherapy). The study will include new patients presenting with primary and specific comorbid insomnia as well as patients with chronic insomnia on treatment.

The research question for the pilot trial is "How well do the procedures and processes designed for conduct of the trial lead to effective implementation of trial including recruitment, randomisation, intervention, and outcome measurements."

The research question for the main trial is as follows "How effective and cost-effective is an educational intervention to primary care teams (general practitioners, primary care nurses and practice managers) to deliver problem focused therapy to adult patients presenting with sleep problems due to lifestyle causes, pain or mild to moderate depression on sleep and quality of life compared with treatment as usual including sleep hygiene and pharmacotherapy?"

The primary hypothesis for the main trial to be addressed is:

"Education for primary care teams in problem focused therapy for patients presenting to primary care with insomnia leads to better sleep outcomes for patients compared to treatment as usual with sleep hygiene up to 3 months from the beginning of treatment."

Secondary hypotheses for the main trial include: "Education for primary care teams in problem focused therapy for patients presenting to primary care with insomnia improves daytime sleepiness, anxiety and depression, health-related quality of life and reduces hypnotic use, adverse effects and costs compared to treatment as usual including sleep hygiene."

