#### Inclusion criteria

1. At least 18 years old.

2. Difficulty initiating and/or maintaining sleep for 1 month or more verified by PSQI score of ≥5.

3. New presentations with insomnia and existing patients on long term hypnotics, over the counter or complementary therapies.

4. 1–3 above and sleep disrupted by painful conditions.

5. 1–3 above and depression measured by the Beck Depression Inventory (BDI score 11–30).

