#### Exclusion criteria

1. Current or previous illicit substance or alcohol abuse.

2. Pregnant or planning pregnancy in the next 12 months

3. Psychotic illness and severe depression defined by a BDI score ≥ 31.

4. Documented or active symptoms of sleep disruptive comorbid conditions e.g. restless legs syndrome and any type of parasomnia.

5. Obstructive sleep apnoea.

6. Terminal Illness.

7. Inability to consent.

8. Current participation in another research study.

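### The protocol assigns anxiety to the Beck Depression Inventory, so the pilot tries out no anxiety measure for the main trial's secondary hypothesis

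*Protocol article*

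**What the plan says.** In Aims, the list that begins "Secondary hypotheses for the main trial include" says that the education "improves daytime sleepiness, anxiety and depression, health-related quality of life and reduces hypnotic use, adverse effects and costs". Anxiety is thus a stated target of the definitive trial.

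In Outcomes, the pilot's secondary measures include "anxiety and depression using the Beck Depression Inventory". One instrument is given for both constructs. No subscale, item set or separate score is named for anxiety.

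In Inclusion criteria, the same inventory serves one purpose: "depression measured by the Beck Depression Inventory (BDI score 11–30" is the text of criterion 5. Exclusion criterion 3 uses a score of 31 or more to define severe depression.

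On who is to be treated, the Abstract refers to patients "presenting with sleep problems due to lifestyle causes, pain or mild to moderate depression or anxiety", and the Background objective refers to "specific comorbid insomnia due to pain or mild to moderate depression and anxiety". The first paragraph of Discussion and conclusion also names anxiety. The main-trial research question in Aims and the second paragraph of Discussion and conclusion mention lifestyle, pain and depression, but not anxiety. Neither list of eligibility criteria mentions anxiety.

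**The concern.** An outcome should be measured with an instrument that the plan treats as measuring it. Here the article names the instrument for anxiety, and that instrument is, by its title and by the article's own use of it, a measure of depression. This is an assignment made in the text, not a detail left to an analysis plan or a fuller protocol.

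The stakes follow from the purpose of the pilot. Study design lists outcome selection and a more accurate sample size among the things it should settle. Without an anxiety measure, the pilot says nothing about completion or variability for that outcome. Data analysis promises the secondary outcomes analyses similar to those of the primary outcome. The Beck score will therefore be modelled as an outcome whose label includes anxiety, although it gives no separate information on anxiety.

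**Working it through.** No arithmetic is needed beyond counting. The check sets the relevant parts of the article side by side.

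**1. Does each construct in the secondary hypothesis have a measure?** With anxiety and depression counted separately, the hypothesis in Aims names seven constructs. Matching them to Outcomes and the health economic section gives:

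| Construct | Measure given |
|---|---|
| Daytime sleepiness | Epworth scale |
| Depression | Beck Depression Inventory |
| Anxiety | Beck Depression Inventory |
| Quality of life | EQ-5D |
| Hypnotic use | Frequency and mean dose |
| Adverse effects | Data Record Book |
| Costs | Resource-use questionnaires |

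Six of the seven have a measure that fits the construct. Anxiety is the one that does not.

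**2. Could another instrument stand in?** Across Participant recruitment and Outcomes, seven instruments are named: PSQI, Beck Depression Inventory, sleep diary, ISI, Epworth scale, EQ-5D and PSYCHLOPS. The article links PSQI, the diary and ISI to sleep, the Epworth scale to sleepiness, EQ-5D to quality of life, and PSYCHLOPS to a psychological outcome profile. Of the six other than the Beck inventory, none is tied to anxiety.

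**3. How does the article itself use the Beck inventory?** At entry, scores of 11 to 30 identify depression that may be included, and scores of 31 or more identify severe depression that is excluded. Both uses concern depression alone. The same total score then appears in Outcomes for anxiety as well, with nothing to separate the two.

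**4. How far does the gap reach?** The planned sample is 4 practices × 20 patients = 80 patients, with outcomes at baseline and at 0, 4, 8 and 13 weeks. In none of these patients, at none of these times, is there a measure specific to anxiety.

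**5. Is anxiety within scope at all?** Three statements of the target population name it: the Abstract, the Background objective, and the first paragraph of Discussion and conclusion. Two omit it: the research question in Aims and the second paragraph of Discussion and conclusion. The inclusion criteria give pain and depression a line each and anxiety none. Where the text speaks of mild to moderate anxiety, nothing defines or bounds it.

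**The case against.** The strongest reply is that the hypothesis belongs to the main trial. The pilot's own research question is about procedures, and because outcome selection is under test, the outcome set can still change. This stands in part. It rules out saying that the pilot fails to test its own hypothesis, and it means that carrying the mislabelled measure into the definitive trial is possible rather than certain. It does not remove the fault. Outcomes fixes what the pilot measures, and a pilot that tries out no anxiety scale cannot inform the choice of one.

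A second reply is that nothing in the article says a Beck difference will be reported as an effect on anxiety. That is correct as far as the reporting goes. The label in Outcomes nevertheless covers anxiety, and that label is what needs correcting.

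Two stronger readings may tempt a reader, and neither is supported:

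- **The silence of the eligibility criteria makes the anxiety hypothesis untestable.** It does not. Inclusion criteria 1 to 3 admit adults with qualifying insomnia whether or not they are anxious. The difficulty lies in the instrument. The silence only leaves the target population unclear.
- **Exclusion 4 may shut anxious patients out.** It reads "Documented or active symptoms of sleep disruptive comorbid conditions e.g. restless legs syndrome and any type of parasomnia", and the abbreviation before the examples leaves the list open. But if it covered every comorbid condition that disturbs sleep, it would also exclude pain and depression, which inclusion criteria 4 and 5 expressly admit. The examples are sleep disorders, and psychiatric exclusions stand separately in exclusion 3.

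**Conclusion.** The point holds as a wrong match between outcome and instrument. Anxiety is assigned to an inventory that the article otherwise uses only for depression, and no other instrument is tied to it.

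Its size is modest: one of seven constructs in the main trial's secondary hypothesis has no measure of its own in the 80 planned patients. Depression is measured, and the primary outcome, PSQI, is unaffected. No sample size, power or significance figure changes. The correction should be made because it is cheap and because choosing outcomes is part of what the pilot is for.

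The conclusion rests on what the article says each instrument is for. The article does not describe the items within the questionnaires, and the conclusion does not depend on them: no item, subscale or score is designated for anxiety.

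The inconsistent statements of the target population are a secondary matter of the same kind. They must be reconciled, but they do not by themselves prevent a test of the anxiety hypothesis.

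**What to change.** Choose one of two routes.

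- **Drop anxiety as an outcome.** In Outcomes, assign the Beck inventory to depression only. In Aims, take anxiety out of the secondary hypothesis. This changes wording only, and the price is one fewer claimed secondary outcome.
- **Keep anxiety as an outcome.** In Outcomes, assign the Beck inventory to depression only and name a separate anxiety scale. Add that scale to the questionnaire pack at baseline and at the same follow-up points as the other measures. The price is one short extra questionnaire for patients.

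Under either route, make the statements of the target population agree: the Abstract, the Background objective, the research question in Aims, the inclusion and exclusion criteria, and both paragraphs of Discussion and conclusion. If anxiety remains a target condition, the article should say how it relates to eligibility. If it does not, the three statements that name it should be changed. This is text editing only.
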